### 9.3.3 Post-Dosing Release Procedures

Following the 7-hour vital sign assessment, if the participant appears to have returned to his/her baseline psychological and physiological state and expresses a readiness to begin the discharge process, the Lead Facilitator and Study Physician/designee will assess the participant for release. This assessment will confirm whether the participant is ready to safely leave the research facility accompanied by his/her support person (family or a trusted friend). This support person will have already been identified and briefed by Facilitators on basic guidelines for accompanying the participant home during preparation session #2. Self-

care activities and additional safety precautions will be reviewed with the participant before the participant and support person leave the premises.

If the participant is experiencing residual study drug effects, such as mild persistent sensorial distortions, he or she will be referred to the Psychiatric Emergency Unit for further observation.

While it is unlikely, if it is found that the participant is experiencing severe persisting physical or perceptual drug effects or is exhibiting signs of significant/severe emotional distress including suicidal ideation, or any other circumstance deemed an emergency per the Study Physician, the Study Physician will refer the participant to the Psychiatric Emergency Unit for further observation.

The participant will be given a post-dosing session summary form which they can use to record recollection of the dosing session before returning for Integration Session #1 on Day 1. This summary may be reviewed with the participant throughout the integration sessions.

#### **9.4 Day 1: Post Dose, Integration Session #1**

The Day 2 visit will occur in person. The purpose of the Day 2 visit is to assess the participant for safety and to allow for integration of the dosing session with the session Facilitators. This visit may take place at the MRI site for the convenience of the subject.

##### **9.4.1 Day 1 MRI (+3 days)**

At day 2 the MRI protocol will be repeated. The same sequences will be repeated (see paragraph 15.).

#### **9.5 Day 8 (-1/+2 days) and 15 (+2 days)**

Day 9 consists of collection of the primary study outcome as well as other safety and efficacy outcomes, and Day 16 allow for continued safety and efficacy follow-up. These visits will occur in person.

##### **9.5.1 Day 15 post dose PET2 and biomarker sampling ( $\pm 7$ days).**

At day 16 PET2, LP2 and blood sampling 2 will occur at the PET-center. All procedures are identical to the #1 occasion.

##### **9.5.2 Day 8 and 15 Integration Sessions #2 and #3**

The purpose of these visits is to allow for further integration of the dosing session together with the dosing session Facilitators. These visits take place in person unless specific circumstances do not allow the participant to attend in person. In that case, video conferencing or phone calls will be arranged.

#### **9.6 Day 42: Post Dose ( $\pm 3$ days)**

This visit will occur in person at Mottagningen för Hjärnstimulering or Affektiva Mottagningen I/II.

Whenever possible, participants who have withdrawn from the study but agree to follow-up will also complete this assessment.

At this time point the patient will be referred for follow up treatment of MDD in accordance with regional treatment guidelines [https://psykiatristod.se/regionala-  
vardprogram/depression](https://psykiatristod.se/regionala-vardprogram/depression)

The patient will be kept blinded to the actual treatment received.

### **9.7 Monthly evaluations, visits from day 43 to 365 and**

Each participant will report MADRS-S and EQ-5D data monthly ( $\pm 5$  days) from day 43 to day 365.

### **9.8 Day 360 Post dose ( $\pm 14$ days) End of study visit**

This visit will occur in person at Mottagningen för Hjärnstimulering or Affektiva Mottagningen I/II. Rating scales used: MADRS, GAD-7, EQ-5D, SDS, AAQII, MLQ, LEQ and CGI (table 1).

Whenever possible, participants who have withdrawn from the study but agree to follow-up will also complete this assessment.

### **9.9 Add on antidepressant treatment**

From day 43, as determined by the patients physician (see 9.7), the patient shall be treated in accordance with regional guidelines: [https://psykiatristod.se/regionala-  
vardprogram/depression](https://psykiatristod.se/regionala-vardprogram/depression)

Information on any treatment that has occurred from day 43 to 365 will be extracted from patient records after day 365. Differences in duration (days) until initiation of antidepressant treatment between treatment groups will be analyzed.

### **9.10 Blinding Related to Delivery of Study Interventions and Collection of Outcome Data**

In order to secure blinding for remaining patients in the study, no patient will receive information of the actual treatment received, with the exception of a serious adverse event, and then at the discretion of the PI or designee.

As with any interventions that produce noticeable psychological effects following administration, blinding psilocybin poses unique challenges.

Prior to start-up, all study site staff will receive extensive training in basic research principles of maintaining the study blind and ensuring only appropriate personnel have access to this information.

Session Facilitators, who will be in the room with participants throughout their dosing sessions, may become functionally unblinded as a result of participants demonstrating changes in behavior and/or speech suggestive of a psychedelic experience, or as a result of participants not demonstrating these types of changes. They will receive written information not to share their thoughts on the outcome of randomization with anyone.

### **9.10.1 Unblinding Procedure**

Full blinding of study personnel and participants will be maintained until data lock at the conclusion of day 365 for all participants, follow-up study physicians and nurses.

Exceptions on an individual subject basis will be made in cases in which it is determined by the PI, the Medical Monitor or the Sponsor that unblinding of a participant's intervention assignment is required for participant safety. Anyone requesting individual unblinding prior to study-wide unblinding will first be referred to the site PI. The site PI must notify the medical monitor of the request and discuss the circumstances surrounding the request. The medical monitor will notify the Sponsor of the request and if unblinding occurred. Attempts should be made to maintain the blind of the investigators prior to the study-wide unblinding. Unblinding during the study will be recorded on the Protocol Deviation Form. All instances of unblinding must be reported to the site IRB and the Sponsor.

#### **9.10.1.1 Interim analysis**

After day 43 visit is completed for the last patient, data from phase A supporting the primary and secondary objectives will be made available to the statistician for analysis. No clinical staff, or PI, who may have future contact with the participants before day 365 will be unblinded. Aggregated results will be presented in a Clinical Study Report but individual data will not be listed.

### **9.11 Early Termination Visit**

Should a participant terminate early, including Prep Phase Terminations and participants who are randomized and later terminate or are terminated for safety reasons, the End of Study visit (day 365) assessments will be completed to the extent possible within 14 days. The End of Study Plan will be discussed at the termination/End of Study visit. An End of Study visit will not be conducted for Screen Failures.

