### **8.5.4 PET1**

The first [C]UCB-J PET examination will take place after LP and before dosing (1-7 days). The examination will be performed at the PET-center at Karolinska Solna and the visit including preparations will take approximately 3 hours. At the visit a rater based MADRS and blood sampling will be performed. Urine samples for toxicology and, if applicable, pregnancy, will be analysed prior to the PET examination.

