## **10. STUDY DISCONTINUATION AND COMPLETION CRITERIA**

### **10.1 Screen Failures**

Screen Failures are defined as participants who are deemed ineligible either at the in-person Screening or Baseline assessment. Screen failures may fail to meet one or more Inclusion Criteria and/or may meet one or more Exclusion Criteria or withdraw consent. Screen Failures may be identified by various ways, including review of medical history, assessments, measures, laboratory results, or conversations with the participant. Medical assessments may be repeated for confirmation. At any time during Screening, if a potential participant is deemed to be ineligible and therefore qualify as a Screen Failure, study personnel will notify the potential participant that he/she is not eligible and no additional Screening assessments will be scheduled or conducted. All potential participants who begin

Screening will be tracked in the EDC study database and reasons for Screen Failure will be recorded.

At the discretion of the site PI or Study Physician, participants who screen fail may be eligible to be re-screened.

Screen Failures may request or be referred to an outside mental health clinician/ medical provider or to their health care provider, if needed.

Screen Failures are not considered evaluable.

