## **10.4 Early Termination Post-Baseline and Pre-Randomization (Preparation Phase Termination)**

It is possible that participants will discontinue study participation between the end of the Baseline assessments and up to randomization on the morning of dosing. This might occur for any of following reasons, including, but not limited to, a decision to withdraw, a decision on the part of site personnel to withdraw the participant prior to dosing, a change in mental or physical health status, or become ineligible to be randomized during the preparatory sessions. These participants will be considered Preparation Phase Terminations and will complete an End of Study visit within 14 days. Similar to Screen Failures, these participants will not be included in the FAS analysis population but will be included in the safety analysis set.

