#### **10.4.3 Dropouts**

If a participant withdraws consent, they will be terminated from the study without further follow up. These participants are defined as dropouts. If they withdraw consent prior to or during Baseline they are considered Screen Failures. If they withdraw consent post dosing then study records/data generated until the date consent is withdrawn will remain available for use by the Sponsor and PI.

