#### **14. SAMPLING AND ANALYSIS OF CEREBROSPINAL FLUID**

Cerebrospinal fluid (CSF) (5 ml) will be sampled at two occasions, between screening visit and Baseline (CSF1), and at PET2 (CSF2). Samples will be analysed for monoamines, monoamine metabolites, cytokines, kynurenic acid and related potential response markers to psilocybin treatment of MDD including genetic markers. Samples will be kept for ten years to enable additional analyses of the same research questions with future, improved methods.

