## 16.2 Populations for Analyses

Efficacy analyses of primary, secondary and exploratory outcomes will be conducted using the FAS population and the Safety set will be used in all safety analyses.

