### *Safety set*

All participants who have received study treatment will comprise the overall safety set.

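### The dosed-only Safety set contradicts the planned pre-dose safety table, and people stopped at Baseline after a lumbar puncture have no scheduled adverse-event inquiry

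*Protocol*

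**What the plan says.** **Analysis set.** Protocol 16.2 defines the set by dosing: "All participants who have received study treatment will comprise the overall safety set". It also fixes its use: "the Safety set will be used in all safety analyses". Section 5.2 of the statistical analysis plan repeats both rules.

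**Undosed people.** Protocol 10.4 covers those who stop after the Baseline assessments but before randomization. They "will be considered Preparation Phase Terminations and will complete an End of Study visit within 14 days", and the same section places them outside the FAS but inside the safety set. Protocol 16.4.6 says that safety data from Screening through Baseline and from the Preparation Phase will be shown apart from post-dose data.

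**Screen Failures.** Protocol 10.1 extends the label to Baseline: "Screen Failures are defined as participants who are deemed ineligible either at the in-person Screening or Baseline assessment". Protocol 10.4.3 adds withdrawals of consent: "If they withdraw consent prior to or during Baseline they are considered Screen Failures". Protocol 9.11 then says: "An End of Study visit will not be conducted for Screen Failures".

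**Procedures and AE collection.** Protocol 8.5.4 puts PET1 after the lumbar puncture and 1 to 7 days before dosing. Section 14 puts the first CSF sample between the screening visit and Baseline. Section 12 describes the arterial line. Protocol 18.5 monitors AEs from signature of the consent form.

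**The concern.** Lumbar puncture and arterial-line PET are the most invasive pre-dose procedures in this trial. Section 17.6 names post-puncture headache as a risk and foresees an epidural blood patch if it persists; 17.5 and 17.7 list risks of cannulation and of the tracer. These harms arise from the procedure, so the people at risk are all who underwent it, dosed or not.

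The protocol ties both the safety denominator and the closing visit to other things: receipt of study drug, and whether a person stopped during Baseline or just after it. At stake are the completeness of the pre-dose AE table, the interpretability of any procedure AE rate taken from it, and whether a delayed procedure complication is ever asked about in someone who leaves before dosing.

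**Working it through.** No figure in the plan needs reproducing. The check sets the rules side by side.

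1. **Membership.** Preparation Phase Terminations stop before randomization, so none has received study treatment. Under 16.2 none can be in the Safety set; under 10.4 all are. Both statements cannot hold.

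2. **The pre-dose table.** 16.4.6 promises pre-dose safety data. If every safety analysis uses the 16.2 set, that table covers only the pre-dose period of people who were later dosed. Section 5.7 of the statistical analysis plan does not repair this. It introduces its summaries as treatment-emergent events, and Protocol 18.1.2 counts events with onset after study drug as treatment-emergent.

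3. **Order of procedures (Table 1).** LP1 is at nominal Day -10, PET1 at nominal Day -3, the second eligibility check on Day -1 and dosing on Day 0. LP1 to PET1 is 10 - 3 = 7 days, and LP1 to dosing is 10 days. Anyone stopped at the PET1 visit has therefore had LP1. One qualifier: Table 1 has no Baseline column, and the Synopsis places CSF sampling and PET at Baseline while section 14 places CSF before it. Prior LP1 is thus likely, but not certain, for every Baseline failure.

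4. **Who has also had PET1.** Urine toxicology and pregnancy tests are analysed before the scan (8.5.4). From Baseline on, the MADRS interview precedes the other outcome assessments (5.6.2), so the suicidality item should be known early. Most Baseline failures would therefore have had LP1 only. A finding or withdrawal during or after the scan would add the arterial line and tracer.

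5. **AE interviews (Table 1).** They are tabulated at Days 0, 1, 8, 15 and 42, with none on the LP1 or PET1 day. Day 365 is blank too, and the row totals confirm it: Day 42 takes 26 minutes and Day 365 takes 23, and 26 - 23 = 3 minutes is the length of the AE interview. Since 9.11 builds the early-termination visit from the Day 365 assessments, that visit contains no tabulated AE interview either.

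| Group | Procedures by then | End of Study visit | Tabulated AE interview after them | Safety set, 16.2 | Safety set, 10.4 |
|---|---|---|---|---|---|
| Ineligible at Baseline | LP1 likely, PET1 sometimes | No | No | No | Unclear |
| Preparation Phase Termination | LP1 and PET1 | Within 14 days | No | No | Yes |
| Dosed | LP1 and PET1 | Yes | Yes, from Day 0 | Yes | Not addressed |

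The entry marked unclear reflects 10.4, which likens Preparation Phase Terminations to Screen Failures in a sentence that can be read as covering the safety set as well as the FAS. 16.2 excludes Screen Failures in any case.

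**The case against.** The strongest reply is that the protocol already captures these harms. AEs and SAEs are recorded from consent (Synopsis, Unsolicited Adverse Events; 18.5), SAEs are reported even when only a procedure is involved (18.6), everyone who starts Screening is tracked in the database (10.1), and unscheduled visits are available (9.12). Someone stopped at PET1 is seen in person by a physician after LP1. The visit denied to Screen Failures has no tabulated AE interview, so their disadvantage against Preparation Phase Terminations is smaller than it looks. The safety objective compares two arms, and unrandomized people have no arm. Withdrawal of consent ends follow-up at any stage under 10.4.3.

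Most of this stands. A reader might infer that pre-dose harms are lost; the documents do not support that, because volunteered events and all SAEs remain recordable. A reader might also infer that the Screen Failure label alone causes the gap. It does not, since nobody has a tabulated AE interview before Day 0. Nor is it supported that Baseline failures have generally had the arterial line.

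A reader might try to size the problem as 30/(1 - f) - 30 for a Baseline failure fraction f. With f at 10%, 20% or 30% this gives 3.3, 7.5 or 12.9 people. Those fractions have no source in the documents, and the formula counts every loss after LP1 as a Screen Failure, although some would be Preparation Phase Terminations. It should not be used as an estimate.

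The reply leaves two things unanswered. Tracking reasons for failure is not asking about AEs, and a visit with no AE question on its schedule is not ascertainment. And 16.2 still conflicts with 10.4 and 16.4.6.

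**Conclusion.** The point holds in a limited form. The safety population is contradictory as written: dosed participants only in 16.2, undosed participants included in 10.4, and a pre-dose presentation in 16.4.6 that 16.2 would strip of everyone undosed. Separately, people found ineligible at Baseline have no End of Study visit and no scheduled AE inquiry after LP1 or PET1. Their events can be recorded if volunteered or serious, but they are not actively sought and belong to no analysis population.

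The size cannot be estimated, because the documents give no Baseline failure rate. The conclusion assumes that 16.2 is applied as worded and that the visit order is that of Table 1. It does not touch the between-arm safety comparison, for which a dosed set is appropriate. Because it changes who is counted, it is more than a detail that could be left to later documentation.

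**What to change.** Reconcile Protocol 9.11, 10.1, 10.4, 16.2 and 16.4.6, and section 5.2 of the statistical analysis plan, as follows.

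- Define a separate pre-dose (procedure) safety population: all consented participants who had LP1 or PET1. Use it for the pre-dose AE table of 16.4.6. Keep the dosed Safety set for comparisons between arms, and correct 10.4 to match.
- Add a brief AE inquiry, for which a telephone call suffices, within the 14 days that 9.11 already uses. It applies to anyone who had LP1 or PET1, is not dosed, and has neither withdrawn consent nor refused contact.
- Write the AE inquiry into the text explicitly. Extending the End of Study visit to these people would not be enough, because the Day 365 assessments carry no tabulated AE interview.

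The cost is a few telephone contacts and one table with a different denominator, in a short amendment. No extra staff or procedure is needed.

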### **9.12 Unscheduled Visits**

Unscheduled visits are any visits conducted to perform additional procedures other than regularly scheduled visit procedures, including additional integration sessions, if needed. Procedures performed will be based on the clinical judgment of the PI, Study Physician, or session Facilitators. Procedures and results will be recorded as an Unscheduled Visit.

## **10. STUDY DISCONTINUATION AND COMPLETION CRITERIA**

### **10.1 Screen Failures**

Screen Failures are defined as participants who are deemed ineligible either at the in-person Screening or Baseline assessment. Screen failures may fail to meet one or more Inclusion Criteria and/or may meet one or more Exclusion Criteria or withdraw consent. Screen Failures may be identified by various ways, including review of medical history, assessments, measures, laboratory results, or conversations with the participant. Medical assessments may be repeated for confirmation. At any time during Screening, if a potential participant is deemed to be ineligible and therefore qualify as a Screen Failure, study personnel will notify the potential participant that he/she is not eligible and no additional Screening assessments will be scheduled or conducted. All potential participants who begin

Screening will be tracked in the EDC study database and reasons for Screen Failure will be recorded.

At the discretion of the site PI or Study Physician, participants who screen fail may be eligible to be re-screened.

Screen Failures may request or be referred to an outside mental health clinician/ medical provider or to their health care provider, if needed.

Screen Failures are not considered evaluable.

## **10.2 Evaluable Participants**

A participant is considered evaluable and eligible for the FAS analysis if he or she meets study eligibility criteria and is randomized to psilocybin or active placebo.

## **10.3 Early Termination from the Study**

Participants can withdraw consent or terminate from the study at any time at his/her request without prejudice. Study personnel can withdraw a participant if, in their clinical judgment, it is in the best interest of the participant or if the participant cannot comply with elements of the protocol that are critical for safety or for the scientific integrity of the study. If study personnel withdraw a participant from the study, study personnel will explain the reason for withdrawing the participant. The reason for early termination will be recorded.

Randomized participants who prematurely terminate from the study will not be replaced.

## **10.4 Early Termination Post-Baseline and Pre-Randomization (Preparation Phase Termination)**

It is possible that participants will discontinue study participation between the end of the Baseline assessments and up to randomization on the morning of dosing. This might occur for any of following reasons, including, but not limited to, a decision to withdraw, a decision on the part of site personnel to withdraw the participant prior to dosing, a change in mental or physical health status, or become ineligible to be randomized during the preparatory sessions. These participants will be considered Preparation Phase Terminations and will complete an End of Study visit within 14 days. Similar to Screen Failures, these participants will not be included in the FAS analysis population but will be included in the safety analysis set.

### **10.4.1 Early Terminations Post-Randomization and Pre-Dosing**

Randomization is to take place immediately before dosing. If a participant is terminated or withdraws post-randomization but prior to dosing, the reason for termination will be documented and the participant terminated.

